## Study treatment

Day 1 is defined as the day the patient presents to the hospital. He undergoes a physical examination, vital signs are documented, and an abdominal ultrasound investigation is performed to confirm the diagnosis of acute cholecystitis. A blood sample is also taken for standard laboratory diagnosis (including Na, K, INR, Hb, platelets, leukocytes, bilirubin, ALT, AST, gamma-GT, AP, amylase, lipase, urea, creatinin and CRP). All relevant concomitant diseases (e.g. coronary heart disease, diabetes mellitus) indicative for morbidity and mortality are recorded [28].

The patient is informed about the trial and is given the opportunity to participate. After the patient has given his informed consent, he is randomized, and all baseline findings, date of birth, age, sex, medical history, height and weight are documented in the CRF.

All patients are examined daily while in the hospital. The laboratory investigations are repeated on Day 3. Samples are taken for microbiological cultures, if necessary. At Day 75 (test-of-cure visit), all diagnostic procedures and treatments between Day 1 and Day 75 are documented. The laboratory determinations and physical examination are repeated, and vital signs are measured. Morbidity is documented according to Table 2.

**Table 2 T2:** Morbidity Score

Persistent abdominal pain > 72 h	1	Pain treated by morphine or derivatives > 72 h
Persistent fever > 72 h	1	Rectal temperature > 38.5°C at least twice
Persistently raised signs of infection > 72 h	1	Persistently elevated CRP or leukocytosis
Wound-healing disorder	2	Any problem leading to re-opening of the wound with subsequent open wound treatment
Thrombosis	3	New onset of leg or pelvic thrombosis
Bleeding	3	Need for more than two bags of packed red cells during or after surgery
Cholangitis	3	New increase in AP, GGT (>2× ULN), bilirubin (>1× ULN) plus leukocytosis (> 12 × 10^3^/μl) or increase in CRP (> 5× ULN)
Icterus	3	New increase in bilirubin, AP and GGT (>2× ULN)
Bile leakage	3	Persistent leakage shown by CT, MRI or ERCP
Abscess	3	Shown by CT, MRI or ultrasound
Pneumonia	3	Shown by X-ray plus drop in arterial pO_2 _plus clinical signs of pneumonia plus leukocytosis plus increased CRP
Embolic lung disease	4	Increased PA pressure (echocardiogram), TNT/TNI, D-dimers
Peritonitis	4	New occurrence of peritonitis
Pancreatitis	4	Increased pancreatic enzymes (> 3× ULN) plus new increase in CRP (> 5× ULN) plus positive clinical signs
Renal failure	4	Drop in urine production below 500 mL/day plus increased creatinine and urea (> 2× ULN)
Relaparotomy	5	Need for follow-up surgery
Cerebral ischemia or bleeding	5	New neurological symptoms with corresponding to changes in cerebral CT
Myocardial infarction	5	Changes in TNT/TNI with or without changes in the ECG meeting the criteria of STEMI of NSTEMI
Septic shock	5	Leukocytosis (> 12 × 10^3^/μl) or leukopenia (< 4 × 10^3^/μl) plus temperature < 36.5°C or > 38.5°C plus clinical signs
Death	63	(Sum of all complications + 1)

Different complications and side effects that may affect the patients during the study are listed and scored differently in increasing severity. Death as worst outcome is scored the sum of all complications plus 1.

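### Table 2's CT-only cerebral row and its oliguria-dependent renal row can score a confirmed serious complication as 0

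*Protocol article*

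**What the plan says.** The Study treatment section says that morbidity at the Day 75 test-of-cure visit is recorded by Table 2, which has 19 non-fatal rows plus death. The rows at issue are:

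- **Cerebral ischemia or bleeding, 5 points:** "New neurological symptoms with corresponding to changes in cerebral CT".
- **Renal failure, 4 points:** "Drop in urine production below 500 mL/day plus increased creatinine and urea", with a threshold of 2× ULN.
- **Pneumonia, 3 points:** "Shown by X-ray plus drop in arterial" pO2, and in addition clinical signs, leukocytosis and raised CRP.

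Two other rows of the same table take several imaging methods: abscess ("Shown by CT, MRI or ultrasound") and bile leakage ("Persistent leakage shown by CT, MRI or ERCP").

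The Day 1 blood tests are given as an open list ("including Na, K, INR, Hb, platelets, leukocytes, bilirubin, ALT, AST, gamma-GT, AP, amylase, lipase, urea, creatinin and CRP"), and "The laboratory investigations are repeated on Day 3". They are repeated again at Day 75. The section also provides for daily examination in hospital and for recording every diagnostic procedure and treatment from Day 1 to Day 75.

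Secondary endpoint 1 is the Table 2 score; the Discussion section compares its mean between groups by the Wilcoxon rank-sum test, stratified by severity. The primary endpoint is morbidity at the test-of-cure visit, and that sentence does not cite Table 2.

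**The concern.** A severity score should register a serious complication once it is confirmed. Two of the heavier rows can fail to do so because of how they are worded, not because information is missing. One admits a single imaging method where sister rows admit several. The other makes low urine output a necessary condition, so a patient with clearly failing kidneys and preserved urine volume does not qualify. Such a patient can enter the score comparison at 0, alongside patients with an uneventful course.

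This is an equivalence trial, so the direction of error matters. If morbidity is counted through Table 2 and the same share of events is missed in both arms, any true difference looks smaller than it is, which favours a declaration of equivalence.

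**Working it through.** **1. The table's own figure.** Three rows at 1 point, one at 2, seven at 3, four at 4 and four at 5 give 3 + 2 + 21 + 16 + 20 = 62. Adding 1 gives 63, the stated death score. The table is internally consistent on weights; the problem lies in the row criteria.

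**2. Test cases read literally against the rows.**

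| Case | Own row met? | Other rows | Score |
|---|---|---|---|
| New deficit, lesion on MRI, no CT change | No: CT change required | None need apply | Can be 0 instead of 5 |
| Creatinine and urea above 2× ULN, urine above 500 mL/day, with or without dialysis | No: urine below 500 mL/day required | None need apply | Can be 0 instead of 4 |
| Infiltrate on X-ray, clinical signs, leukocytosis, raised CRP, no recorded fall in arterial pO2 | No: fall in pO2 required | Fever beyond 72 h (1); CRP or leukocytes raised beyond 72 h (1) | Often 1 or 2 instead of 3; 0 only if neither persists |

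**3. Consistency across rows.** Abscess and bile leakage accept MRI; the cerebral row does not. Nothing in the article explains the difference.

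**4. Which analyses are touched.** Secondary endpoint 1 uses Table 2 explicitly, so its Wilcoxon comparison is affected on any reading. For the primary endpoint the link is an inference: Study treatment ties Day 75 morbidity to Table 2, and the article gives no other definition of morbidity, but nowhere does it say that the primary event is any Table 2 row.

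**5. How a missed share would act on the equivalence test.** This is an illustration only, because the documents give no rate for these complications.

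Inputs from the article: 273 evaluable patients per group, 16% expected morbidity, a 10-point margin, and equivalence declared only if the 95% CI lies within ±10 points. Assumptions: a true difference exactly at the margin (26% v 16%); the same share f of patients with morbidity missed in both arms; an unstratified normal approximation.

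Observed rates are p1 = 0.26(1 − f) and p2 = 0.16(1 − f), with D = p1 − p2 and SE = √[p1(1 − p1)/273 + p2(1 − p2)/273].

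P(declare equivalence) = Φ[(0.10 − D)/SE − 1.96] − Φ[(−0.10 − D)/SE + 1.96].

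For f = 5%: p1 = 0.247, p2 = 0.152, D = 0.095, SE = 0.0340. The first term is Φ(0.147 − 1.96) = Φ(−1.813) = 0.035; the second is negligible.

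| f | Patients missed (26% arm / 16% arm) | Observed difference (points) | Chance of wrongly declaring equivalence |
|---|---|---|---|
| 0 | 0 / 0 | 10.0 | 2.5% |
| 5% | 3.5 / 2.2 | 9.5 | 3.5% |
| 10% | 7.1 / 4.4 | 9.0 | 4.8% |
| 20% | 14.2 / 8.7 | 8.0 | 9.1% |

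Patients missed are f × 0.26 × 273 = f × 71.0 and f × 0.16 × 273 = f × 43.7. Here f covers only patients whose sole event is one that fails its row. Two rows out of 19 are at issue, so a large f is hard to credit. If the true rates are equal, equal under-counting leaves the difference at zero.

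**The case against.** **The work-up.** A reader might infer that these rows demand tests the trial does not perform, since blood gas, urine volume and cerebral CT are absent from the listed tests. The document does not support that. The laboratory list is open, these are tests ordered when a complication is suspected, and all diagnostics to Day 75 are recorded. The embolism and infarction rows also rest on tests outside the list (echocardiogram, troponin), and a condensed article may leave such detail to the full protocol. This objection stands in full. It does not rescue the two rows: recording an MRI does not satisfy a CT-only criterion, and recording creatinine or dialysis does not satisfy an oliguria criterion.

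**Pneumonia.** A reader might infer that an X-ray-proven pneumonia without a documented fall in pO2 counts as no morbidity. Usually it would not, because the 1-point fever and inflammatory-marker rows remain available; in a yes/no endpoint based on any Table 2 row, that patient would then be counted. Strict criteria also have value in a non-blinded trial, where they limit discretionary event calling. With misclassification equal in both arms, the observed difference shrinks by the factor (sensitivity + specificity − 1), so lost specificity pulls toward equivalence as well. Whether to relax the pO2 condition is therefore a judgement call, and no change is asked for.

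**Severe events in general.** It would be tempting to call the table least sensitive for severe events. It is not so overall: infarction counts with or without ECG changes, and relaparotomy and peritonitis have permissive rows.

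**The primary endpoint.** The effect there is inferred, as set out above, and this limit stands.

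**Conclusion.** The point holds for two rows. As worded, an MRI-proven stroke without CT changes and renal failure without oliguria can each score 0 in Table 2, where 5 and 4 points are intended. The CT-only wording is also inconsistent with the abscess and bile leakage rows. The pneumonia row mainly under-scores.

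The Table 2 score is affected directly. An effect on the primary comparison assumes that the primary event is counted through Table 2. Any pull toward equivalence further assumes a true difference and a similar missed share in both arms. Its size cannot be derived from the documents and is probably small: even a 5% missed share moves the false-equivalence risk only from 2.5% to 3.5%.

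A reader might try to size the effect as a loss in one arm. One missed patient is 1/273 = 0.37 points. At 16% the CI half-width is 1.96 × √(2 × 0.16 × 0.84/273) = 6.15 points, which leaves 10 − 6.15 = 3.85 points for the observed difference. Assuming that 1–3% of an arm has such an event alone and that half are missed, 0.5–1.5 points are lost, or 13–39% of that allowance. The arithmetic is right, but the document supports neither the rates nor a loss confined to one arm. A one-arm loss is also a different mechanism: it could create a difference as easily as hide one.

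**What to change.** Edit two lines of Table 2 and the matching CRF key:

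1. **Cerebral row:** new neurological symptoms with corresponding changes on cerebral CT or MRI.
2. **Renal row:** keep the present criterion and let the row also be met by new renal failure without oliguria, that is creatinine and urea above 2× ULN, or new dialysis recorded by Day 75. The laboratory threshold is the row's own. New should mean absent at Day 1, which can be checked because creatinine and urea are in the Day 1 blood tests; otherwise long-standing renal impairment would be counted.

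Leave the pneumonia row as it is unless the investigators decide that a more sensitive definition is worth the loss of specificity.

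The weights do not change, so the rows still sum to 62 and the death score stays 63. No new test is needed. The downside is a slightly less specific renal row.

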### Procedure for patients receiving immediate surgery

• Laparoscopic cholecystectomy in the 24 hours after hospital admission

• Antibiotic therapy with moxifloxacin 400 mg i.v. once per day for 48 hours followed by oral Moxifloxacin 400 mg daily or discontinuation of antibiotic treatment if possible

• Discharge of the patient as soon as possible after Day 2, if the body temperature, CRP and leukocytes are normal

• Test-of-Cure visit at Day 75

### Procedure for patients receiving primarily conservative therapy with elective surgery

• Therapy with i.v. moxifloxacin 400 mg once daily for 48 hours followed by oral moxifloxacin 400 mg per day. Discontinuation of moxifloxacin after Day 7, provided body temperature, CRP and leukocytes are normal

• Discharge of the patient as soon as possible after Day 4 on oral moxifloxacin

• Elective cholecystectomy between Days 7 and 45 after admission to study using single-shot moxifloxacin i.v. for prophylaxis

• Test-of-Cure visit at Day 75

## Primary and secondary endpoints

### Primary endpoints

Primary endpoint is morbidity at the test-of-cure (TOC) visit (75 days after trial inclusion) in the tested population valid for efficacy.

### Secondary endpoints

1. Morbidity over 75 days using the scoring system showed in Table 2

2. Morbidity 3 days after cholecystectomy (immediate and elective)

3. Rate of conversion from laparoscopic to open surgery

4. Change of antibiotic due to non-response or non-toleration of moxifloxacin

5. Mortality at Day 75

6. Cost-efficiency

7. Hospital time

8. Safety and tolerance of moxifloxacin

9. Duration of hospital stay after cholecystectomy (days)

## Adverse events and serious adverse events

Adverse events and serious adverse events and deaths occurring up to Day 75 were recorded. An adverse event (AE) is every medical event that worsens or impairs the well-being of the patient not being part of the natural course of the disease but may be due to treatment or drug application. The term AE can cover any sign, symptom or reaction, including not normal laboratory findings, independent if caused by the tested procedure and medication or not. Adverse event intensity (mild, moderate or severe) and relationship to the treatment or the study drug moxifloxacin (probable, possible, unlikely or none) were categorized. Serious adverse events (SAEs) included those events that were fatal, life-threatening, required hospitalization, resulted in disability or otherwise endangered the patient.

All AEs and SAEs will be documented in detail in the case report form (CRF) and will be reported to the principal investigator at regular intervals. SAEs have to be reported within 24 hours to the principal investigator, and must be documented separately on an SAE report form within 24 hours. According to law and guidelines, SAEs have to be reported to the ethics committee(s) and supervisory board(s) as necessary. The period of observation for AE reporting is from Day 1 to Day 75.

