## Background

### Medical problem

Acute cholecystitis is one of the most significant acute diseases in the Western World, and may be associated with only mild pain and nausea or become a severe, life-threatening illness due to complications. Acute cholecystitis is mainly caused by gall stones, whilst cholestasis is mainly associated with superinfection with bacteria, in general species of enterobacteria, enterococci, bacteroides and anaerobic streptococci [1].

The principal complication is recurrent biliary colic and cholestasis. The latter may lead to ascending cholangitis, and whilst this can be managed with antibiotics, other complications can not be cured conservatively, such as gangrenous changes, gall bladder perforation and biliary leakage, and acute necrotic gallstone pancreatitis [2-5]. Liver abscesses and underlying incidental carcinoma have also been reported in some cases [2,6].

The risk of developing second and subsequent episodes of acute cholecystitis is higher than the risk of suffering an initial episode [7,8]. Laparoscopic cholecystectomy is therefore usually recommended, but whether this should be performed immediately or after first giving antibiotic treatment to allow the acute condition to subside is controversial [9-12].

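### The adverse event definition can leave biliary recurrences before surgery out of the AE and SAE record, and these arise mainly in the delayed-surgery arm

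*Protocol article*

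**What the plan says.** All the wording at issue stands in the protocol article, section Adverse events and serious adverse events.

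- The sentence that defines an AE takes any medical event that harms the patient's well-being and limits it to events "not being part of the natural course of the disease but may be due to treatment or drug application".
- The sentence after it extends the term to any sign, symptom, reaction or abnormal laboratory finding, "independent if caused by the tested procedure and medication or not".
- Causality is then graded: "relationship to the treatment or the study drug moxifloxacin (probable, possible, unlikely or none) were categorized".
- SAEs are said to include events that were "fatal, life-threatening, required hospitalization, resulted in disability or otherwise endangered the patient". They must be reported to the principal investigator within 24 hours.
- One window applies to everyone: "The period of observation for AE reporting is from Day 1 to Day 75".

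The arms differ in how long the diseased organ stays in place. The immediate arm is operated on within 24 hours of admission. The procedure for the conservative arm allows discharge after Day 4 and then sets "Elective cholecystectomy between Days 7 and 45 after admission to study".

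**The concern.** The article names recurrent biliary colic and cholestasis as the principal complication of the disease. It adds: "The risk of developing second and subsequent episodes of acute cholecystitis is higher than the risk of suffering an initial episode". Avoiding recurrent cholecystitis or pancreatitis is also what its Background offers as the possible gain from early surgery. Recurrence while waiting is therefore one of the harms that separates the two strategies, and it is also the event most naturally described as the disease running its course.

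An investigator who follows the defining sentence could leave such an event off the AE form. One who follows the next sentence would record it. With about 30 sites planned, both readings could be in use at once. What is at stake is whether AE and SAE rates can be compared between arms, and whether a recurrence is reported within 24 hours. The secondary endpoint on safety and tolerance of moxifloxacin also needs one rule, because infection that persists or returns on the drug could be filed either as disease course or as an AE.

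**Working it through.** No arithmetic applies, because the point concerns wording and rests on no rate or sample size. The check applies each rule to example events and then asks who is exposed to them.

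**Step 1: how far the two sentences conflict.** The defining sentence sets two conditions: the event lies outside the natural course, and it may be due to treatment. The next sentence drops the need for a treatment cause, and the causality grade of none fits that. So the second condition conflicts with what follows. The first condition does not conflict logically, since lying outside the natural course and being caused by treatment are separate properties. What stays open is the status of a disease complication.

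**Step 2: example events under each rule.**

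| Event | Defining sentence | Next sentence | Table 2 (Morbidity Score) |
|---|---|---|---|
| Wound reopened after surgery | AE | AE | 2 points |
| Unrelated intercurrent illness | Not natural course, but fails the treatment condition if read strictly | AE | Only if a listed item |
| Biliary colic at home before surgery, resolved within 72 h | Can be excluded | AE | No item |
| Recurrent cholecystitis before surgery, pain and fever resolved within 72 h | Can be excluded | AE | No item of its own; scores only if another item is met |
| Biliary pancreatitis before surgery | Can be excluded | AE | 4 points if the enzyme, CRP and clinical criteria are met |

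The operative complication is an AE under either sentence. The three pre-operative biliary events depend on which sentence the site follows.

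**Step 3: whether Table 2 fills the gap.** It has no natural-course exclusion, and it lists cholangitis, icterus, pancreatitis, peritonitis, abscess and persistent pain, fever or infection signs beyond 72 h. It has no item for recurrent colic, recurrent cholecystitis or gall bladder perforation. These score only if they also meet another item. A short recurrence, even one that led to readmission, may score nothing. The Day 75 record of diagnostic procedures and treatments may show that it happened, but not as an AE.

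**Step 4: exposure by arm.** In the immediate arm, a biliary event before surgery is possible only in the interval of up to 24 hours after admission. In the conservative arm it is possible until the operation on Day 7 to 45. The rule and the observation window are the same for both arms, but the time at risk of the excluded kind of event is not.

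**Step 5: serious events.** The section does not say in so many words that an SAE must first be an AE. If it is read that way, a recurrence classed as natural course is not an SAE even when it leads to readmission, and the 24-hour report is not triggered.

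**Step 6: the SAE list.** It names events that "required hospitalization, resulted in disability or otherwise endangered the patient", and does not name prolongation of an existing stay. A complication that only lengthens a stay could then be classed differently from the same complication that causes a readmission.

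**The case against.** The strongest reply is that this is loose drafting with little consequence. Much of it stands.

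- A reader might infer that the two sentences flatly contradict each other. They do not: an intercurrent illness can lie outside the natural course and count whatever its cause. The conflict is partial.
- A reader might infer that the same harm is in fact counted differently in the two arms. The document sets one rule and one window for both. Unequal counting is an inference from unequal exposure, and depends on sites applying the exclusion.
- A reader might infer a threat to the equivalence conclusion, for example by assuming that 5% to 15% of delayed-arm patients have a recurrence (0.05 × 273 = 13.7 and 0.15 × 273 = 41.0 of the 273 evaluable patients) and setting that beside the 10-point margin. The documents do not support this. They give no recurrence rate, and the margin applies to the difference in morbidity rates, not AE rates. Morbidity is documented by Table 2, which does not use the AE definition, and mortality is a separate endpoint.
- The SAE point is weak. The list is introduced as what SAEs included and ends with a general clause on endangering the patient, and a condensed article may shorten wording that the full protocol gives in full. Patients in both arms have hospital stays that can be prolonged and discharges that can be followed by readmission.
- The two effects can run in opposite directions. The exclusion lowers the delayed arm's AE count, while a readmission makes an event there more readily serious. No net direction is shown.

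What the reply does not answer is that the exclusion is stated text, not an omission left to a fuller document, and that Table 2 has no item for the recurrences most exposed to it.

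**Conclusion.** The point holds as a defect in the AE definition. A stated exclusion can remove biliary recurrences before surgery from the AE record, and from 24-hour reporting if SAEs are a subset of AEs. Because mainly the delayed arm can have these events, AE and SAE rates may not be comparable between arms.

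This rests on two assumptions: that at least some investigators would class a recurrence as natural course, and, for expedited reporting, that SAEs are drawn from AEs. The documents confirm neither. No size can be derived from them. The reach is the AE and SAE data and the moxifloxacin safety endpoint; an effect on the equivalence test of Day 75 morbidity is not shown. The wording is worth correcting because the affected events are ones that the trial's own rationale names. The missing mention of prolonged hospital stay is secondary and minor.

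**What to change.** In the section Adverse events and serious adverse events:

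1. Delete the clause that excludes the natural course of the disease and refers to a possible treatment cause.
2. Define an AE as any untoward medical event from Day 1 to Day 75, regardless of cause. The causality grading can stay as it is.
3. State that biliary events before surgery, including recurrent colic and recurrent cholecystitis, are recorded as AEs by the same rule in both arms.
4. As a minor addition, name prolongation of an existing hospital stay among the SAE criteria, and state that the planned admission for elective cholecystectomy is not itself an SAE.

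This changes wording only and leaves the endpoints, sample size and analysis untouched. The cost is more AE and SAE forms for recurrences and prolonged stays.
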